## Abstract

**Background:**

Patients affected by lumbar spinal stenosis (LSS) suffer from a multifactorial degeneration of the lumbar spine resulting in narrowing of the neuroforamina and spinal canal, leading to various functional limitations. It remains unclear whether LSS patients after surgery would benefit from early post-operative rehabilitation, or if a delayed rehabilitation would be more advantageous. The purpose of this partially randomized patient preference trial is to evaluate the impact of post-operative rehabilitation timing as well as surgical intervention type on psychometric properties and functional outcomes in patients with LSS.

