**Methods:**

Data for this patient preference trial are collected before and after surgical (decompression only or decompression and fusion) and rehabilitative interventions as well as six, 12 and 24 months after completing rehabilitation. The study participants are patients diagnosed with LSS who are at least 18 years old. After a medical check-up, participants will complete patient-reported outcome measures (PAREMO-20, SIBAR, FREM-8, SF-12, SFI, ODI) and different functional assessments (functional reach test, loaded reach test, handgrip strength, standing balance control, 6-min walk test).

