## Background

1

Lumbar spinal stenosis (LSS) is a common source of lower-quarter musculoskeletal pain resulting in meaningful limitations of patients’ quality of life. The prevalence of LSS increases with advancing age [1,2] and is expected to be twice as common in adult people older than 65 years [3]. In Europe, with an incidence of 2.2%, 102 million people are thought to be affected annually [4]. Multifactorial degeneration of the lumbar spine resulting in narrowing of the neuroforamina and thus compression of the spinal nerves, leads to symptomatic reduction in walking distance and neurogenic claudication in patients affected by LSS [5].

Therapeutic options depend on the patient's symptoms and concomitant pathologies. However, conservative therapy attempts should be performed first, consisting of physiotherapy, pain therapies, and epidural infiltrations [6]. In case of recurrent symptoms over a period of three to six months after starting conservative treatment, surgical therapy, was found to be superior to continuing conservative therapy only [7]. Available surgical procedures include microsurgical decompression alone, and decompression with fusion using an internal fixator and intervertebral or posterolateral fusion [8]. In post-operative pain and disability, laminectomy with fusion seems to be superior to laminectomy alone [9].

The evaluation of therapy success focuses, among other things, on the progress of walking distance. Alongside pain, walking distance is the leading functional outcome in patients with LSS. However, walking ability and its descriptors used to characterize LSS patients are not homogeneous [10]. Specifically, LSS patients show reduced walking distance, gait velocity and lower extremity strength. Moreover, after a provocation walk (400 feet, approximately 122 m) patients with LSS showed decreased hip flexor and knee extensor strength, which was no longer evident after surgical decompression [11]. Those outcomes were recently found to be moderately to strongly associated with patients' handgrip strength [12]. Thus, handgrip strength seems a promising, easy to record, surrogate measure for functional ability in patients with LSS, especially since radiological findings failed to predict patients’ walking distance [13].

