Functional electrophysiological examinations (surface EMG) of muscles in LSS patients are very rare. However, these can provide concrete evidence of muscular function and coordination and thus detect dysfunction or dyscoordination. A correlational study examining gait and muscle activation characteristics could demonstrate increased paraspinal and gluteal muscle activity in patients with LSS [14]. After decompression surgery, patients showed decreased paraspinal and increased gluteal muscle activation [15]. Unfortunately, co-activity or symmetry were not examined here.

Active rehabilitation one to two months after surgery results in pain reduction and improves overall health in patients with lumbar disk degeneration [16]. However, it remains unclear whether LSS patients would benefit from early postoperative rehabilitation, or if a delayed rehabilitation would be more advantageous. In our regional setting, depending on the preference of the surgeon, both approaches are implemented.

This controlled and partially randomized patient preference trial aims to evaluate the impact of post-operative rehabilitation timing as well as surgical intervention type on psychometric properties and functional outcomes in patients with LSS. To identify predictors for intervention success or failure, patient-related outcome measures, functional tests, and surface EMG measurements will be used.

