#### Statistical analyses

2.3.7

The data collected will be used to answer various research questions. Hence different analyses will be conducted. First, data quality checking will be performed to ensure that discrepancies, errors, or duplicates are excluded from further analyses and overall data consistency is given. Second, data will undergo exploratory data analysis. Finally, depending on the variables available, appropriate statistical tests (e.g., linear regressions, Student's t-tests, Chi^2^-tests) will be applied to uncover differences related with rehabilitation timing after LSS surgery. Statistical analyses will be performed using IBM SPSS 28.0 (IBM Corp., Armonk, NY, USA) software.a)Subjective (ODI, SF-12) and functional performance (handgrip strength, FRT) of early and later post-operative rehabilitation intervention groups will be compared using multivariate general linear mixed model and Chi^2^-test (categorical data, specifying frequencies in percent).b)Subjective and functional performance of surgically (two groups) and conservatively treated patients with LSS and controls without spinal impairments will be compared using multivariate general linear mixed model and Chi^2^-test (categorical data, specifying frequencies in percent).c)Subjective and functional performance before and after the intervention(s) will be compared using multivariate general linear mixed model and Chi^2^-test (categorical data, specifying frequencies in percent).d)Associations of subjective and functional assessments will be tested by means of correlation analyses.

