#### Patient and public involvement (PPI) statement

2.3.8

Early or delayed start of the rehabilitation program will be randomized for the surgically treated patients. If patients don't want to be randomized, they can choose their preferred starting time of the post-surgical rehabilitation program. Control participants will be recruited through public announcements. Furthermore, patients will be encouraged to recruit controls without any known lumbar spinal impairments from their own environment in order to increase the chance of getting comparable control subjects in terms of sex, age, and activity level. Patients' and controls' will be asked about their experience with the assessments in order to better estimate and compare the exhibited strain and perceived exertion of the functional tests.

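### The aim claims an impact of surgery type, which no one allocates; that contrast is observational and should be defined, adjusted and reported as an association

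*Protocol article*

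**What the plan says.** The aim, in the Abstract and again at the end of section 1, is to "evaluate the impact of post-operative rehabilitation timing as well as surgical intervention type on psychometric properties and functional outcomes in patients with LSS". Timing and surgery type are put on the same footing. The Abstract's Methods describe the interventions as "surgical (decompression only or decompression and fusion) and rehabilitative interventions".

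Allocation is described in section 2.3.8: "Early or delayed start of the rehabilitation program will be randomized for the surgically treated patients", and "If patients don't want to be randomized, they can choose their preferred starting time of the post-surgical rehabilitation program". No section says how the type of operation is assigned. The nearest text is a general remark in section 1: "Therapeutic options depend on the patient's symptoms and concomitant pathologies". Section 2.2 says that patients are recruited and treated in two local but independent spinal surgery centres.

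In section 2.3.7, analysis a) compares early with later rehabilitation by a mixed model and a chi-squared test. It does not separate randomised patients from those who chose. Analysis b) says that "surgically (two groups) and conservatively treated patients with LSS and controls without spinal impairments will be compared using multivariate general linear mixed model". No adjustment term is named in either. Section 1 treats surgery type as related to outcome: "In post-operative pain and disability, laminectomy with fusion seems to be superior to laminectomy alone".

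**The concern.** Impact is causal language. It is defensible for rehabilitation timing among randomised patients. For surgery type the article gives no assignment mechanism. If the operation follows symptoms and concomitant pathology, as the general remark in section 1 suggests, patients who receive fusion differ at baseline from those who receive decompression alone, and the case mix may also differ between the two centres. A difference in ODI between the groups then mixes the operation with the reason for choosing it.

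The listed analysis does not resolve this. If the two surgical groups in b) are surgery types, the contrast is listed as a plain group comparison. If they are timing groups, the surgery-type aim has no listed group comparison. A reader following the text could publish a surgery effect that the design cannot support.

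**Working it through.** **1. Aim against allocation**

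| Factor | Stated aim | How assigned in the article | Status of the contrast |
|---|---|---|---|
| Timing, randomised patients | impact | randomised (2.3.8) | unconfounded in expectation |
| Timing, preference patients | impact | patient's choice (2.3.8) | observational |
| Surgery type, all surgical patients | impact | not stated | observational |

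The third row is unchanged if only the randomised cohort is analysed, because the randomisation concerns timing.

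**2. What the sample size supports**

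Inputs from section 2.3.6: mean ODI change 16.1, SD 17.8, alpha 5%, power 95%, responder share 65%, dropout 20%.

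- Effect size: 16.1 / 17.8 = 0.90. A one-sample t-test gives n = 15 if one-sided (power 0.952). A two-sided test at d = 0.90 would need 19.
- Inflation: 15 / 0.65 = 23.1, rounded up to 24; 24 / 0.80 = 30. The stated 30 per group is reproduced.

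This is a calculation of within-group change in fusion patients. It says nothing about a difference between groups. Suppose, as an assumption, that the groups are surgery types, that 30 × 0.80 = 24 per group are evaluable, and that SD 17.8 applies. A two-sided 5% two-sample t-test then has 80% power at d = 0.826, which is 0.826 × 17.8 = 14.7 ODI points. Power for a ten-point difference is 0.48. These figures show imprecision; they are not evidence of confounding.

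**3. Illustrative size of confounding**

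All inputs in this step are assumptions, because the article gives none.

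*Surgery-type contrast.* Bias = baseline ODI difference × slope of follow-up on baseline.
- 5 × 0.3 = 1.5 points
- 10 × 0.5 = 5.0 points

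*Timing contrast, preference patients.* Bias = prognostic difference between surgery types × difference in fusion share between timing groups.
- 60% versus 40%: 5 × 0.20 = 1.0 point
- 75% versus 25%: 10 × 0.50 = 5.0 points

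If half of a pooled sample is randomised and balanced, these halve: 1.0 × 0.5 = 0.5 and 5.0 × 0.5 = 2.5 points.

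*Effect on error rate.* With no true timing effect and SD 17.8, a bias of 4 points (10 × 0.40) raises the 5% two-sided rejection rate to about 12% with 24 per group, or 14% with 30.

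*Timing contrast, randomised patients.* The expected difference in fusion share is zero, so the expected bias is zero. Adjustment there buys precision.

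**The case against.** The strongest reply is that this is a condensed article and that covariate lists belong in the full protocol or the analysis plan. Silence about covariates does not mean the model is unadjusted, and a reader who infers that the groups will be compared raw goes beyond the text. The article names a mixed model, and baseline could enter it as a time level, since analysis c) compares before with after. The design is openly labelled as partially randomised, and section 2.2 provides for monitoring of balance in periodic meetings. All of this stands: a missing covariate list alone would not be a finding.

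Three stronger readings are tempting and are not supported.

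- A reader might infer that the timing contrast is confounded throughout. Among randomised patients, surgery type, hospital and baseline ODI are balanced in expectation.
- A reader might take "In our regional setting, depending on the preference of the surgeon, both approaches are implemented" to mean that surgeons' preferences fix the type of operation, or tie it to timing within the trial. That sentence describes regional practice on rehabilitation timing, and in the trial timing is randomised or chosen by the patient. That surgery type is decided clinically is a fair inference, but it is not stated.
- A reader might say that surgery type is absent from the analyses. It may be the grouping factor in b).

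The reply does not remove the causal aim for an unallocated factor or the undefined groups in b). An analysis plan cannot make surgery type a randomised comparison. The balance monitoring is informal and names neither surgery type nor hospital.

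**Conclusion.** The point holds in a limited form. The article states a causal aim for surgery type, allocates only rehabilitation timing, and pairs the aim with a group comparison whose surgical groups are undefined. The surgery-type result can support an association at most. The timing contrast shares the problem only for preference patients or a pooled analysis. Analysis a) appears to pool, because it does not separate the cohorts.

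The bias of 1 to 5 ODI points illustrates assumed inputs and is not a finding from the article. The upper end for timing needs a 50-percentage-point difference in fusion share, which is not plausible under randomisation. The conclusion about the surgery-type aim does not depend on these figures. It should be corrected before analysis; it does not invalidate the randomised timing comparison.

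**What to change.** 1. In the aim (Abstract and end of section 1), keep impact for rehabilitation timing and speak of the association of surgical intervention type with the outcomes.
2. In 2.3.7 b), say whether the two surgical groups are surgery types. Estimate the surgery-type contrast in ODI from a model adjusted for baseline ODI, age, sex, hospital and rehabilitation timing, plus spondylolisthesis grade if it is recorded. Report it with a confidence interval as an adjusted association.
3. In 2.3.7 a), include baseline ODI, surgery type and hospital in the early-versus-later ODI model. In randomised patients this is for precision; in preference patients it is for control of confounding.

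The cost is a few degrees of freedom: five for the terms in item 2, or six with a two-level spondylolisthesis term, against 2 × 24 = 48 evaluable patients under the assumption above. The surgery-type conclusion becomes more modest, and unmeasured indication can still confound it. No new patients are needed, and the data are largely collected already.

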**Methods:**

Data for this patient preference trial are collected before and after surgical (decompression only or decompression and fusion) and rehabilitative interventions as well as six, 12 and 24 months after completing rehabilitation. The study participants are patients diagnosed with LSS who are at least 18 years old. After a medical check-up, participants will complete patient-reported outcome measures (PAREMO-20, SIBAR, FREM-8, SF-12, SFI, ODI) and different functional assessments (functional reach test, loaded reach test, handgrip strength, standing balance control, 6-min walk test).

**Ethics and dissemination:**

The results of this study will be published through peer-reviewed publications and scientific contributions at national and international conferences. This research has been approved by the Institutional Review Board of Martin Luther University Halle-Wittenberg (reference number: 2022-128).

## Background

1

Lumbar spinal stenosis (LSS) is a common source of lower-quarter musculoskeletal pain resulting in meaningful limitations of patients’ quality of life. The prevalence of LSS increases with advancing age [1,2] and is expected to be twice as common in adult people older than 65 years [3]. In Europe, with an incidence of 2.2%, 102 million people are thought to be affected annually [4]. Multifactorial degeneration of the lumbar spine resulting in narrowing of the neuroforamina and thus compression of the spinal nerves, leads to symptomatic reduction in walking distance and neurogenic claudication in patients affected by LSS [5].

Therapeutic options depend on the patient's symptoms and concomitant pathologies. However, conservative therapy attempts should be performed first, consisting of physiotherapy, pain therapies, and epidural infiltrations [6]. In case of recurrent symptoms over a period of three to six months after starting conservative treatment, surgical therapy, was found to be superior to continuing conservative therapy only [7]. Available surgical procedures include microsurgical decompression alone, and decompression with fusion using an internal fixator and intervertebral or posterolateral fusion [8]. In post-operative pain and disability, laminectomy with fusion seems to be superior to laminectomy alone [9].

The evaluation of therapy success focuses, among other things, on the progress of walking distance. Alongside pain, walking distance is the leading functional outcome in patients with LSS. However, walking ability and its descriptors used to characterize LSS patients are not homogeneous [10]. Specifically, LSS patients show reduced walking distance, gait velocity and lower extremity strength. Moreover, after a provocation walk (400 feet, approximately 122 m) patients with LSS showed decreased hip flexor and knee extensor strength, which was no longer evident after surgical decompression [11]. Those outcomes were recently found to be moderately to strongly associated with patients' handgrip strength [12]. Thus, handgrip strength seems a promising, easy to record, surrogate measure for functional ability in patients with LSS, especially since radiological findings failed to predict patients’ walking distance [13].

Functional electrophysiological examinations (surface EMG) of muscles in LSS patients are very rare. However, these can provide concrete evidence of muscular function and coordination and thus detect dysfunction or dyscoordination. A correlational study examining gait and muscle activation characteristics could demonstrate increased paraspinal and gluteal muscle activity in patients with LSS [14]. After decompression surgery, patients showed decreased paraspinal and increased gluteal muscle activation [15]. Unfortunately, co-activity or symmetry were not examined here.

Active rehabilitation one to two months after surgery results in pain reduction and improves overall health in patients with lumbar disk degeneration [16]. However, it remains unclear whether LSS patients would benefit from early postoperative rehabilitation, or if a delayed rehabilitation would be more advantageous. In our regional setting, depending on the preference of the surgeon, both approaches are implemented.

This controlled and partially randomized patient preference trial aims to evaluate the impact of post-operative rehabilitation timing as well as surgical intervention type on psychometric properties and functional outcomes in patients with LSS. To identify predictors for intervention success or failure, patient-related outcome measures, functional tests, and surface EMG measurements will be used.

## Methods

2

### Study design

2.1

The present study is a partially randomized patient preference trial performed on patients from two different local hospitals. Measurements will be performed before the surgical intervention, at the time when the patient starts standardized rehabilitation, directly after rehabilitation and six, 12 and 24 months after rehabilitation (Fig. 1). For comparative purposes the standardized rehabilitation will be implemented by one local rehabilitation center with similar protocols for the early and late rehabilitation groups. Additionally, a conservatively treated group will be recruited within the rehab center responsible. The study was registered with the German Clinical Trials Register (ID: DRKS00032248). The SPIRIT reporting guidelines were used for this trial protocol [17]. The baseline data collection started in August 2023.

**Fig. 1 fig1:**
[figure not shown]
The study flow diagram highlighting the measurement time points (exams) and early and later post-operative rehabilitation intervention groups (BMT, Bergmannstrost. DOTS, Department of Orthopedic and Trauma Surgery. PT, Physiotherapy). Note the conservatively treated group is not considered.

### Study participants

2.2

The study participants are at least 18 years old. An overview of the inclusion and exclusion criteria is given in Table 1. Patients suffering from LSS will undergo surgical intervention or conservative treatment with a standardized rehabilitation program at the same rehabilitation center for three weeks (15 intervention sessions each lasting 4 to 5 h). LSS patients will be recruited and treated in two local but independent spinal surgery centers. The conservatively treated group will be enrolled at the rehab center. Patients meeting the inclusion criteria listed in Table 1 will be included consecutively in the study. Control participants will be recruited through public announcements. Furthermore, patients will be encouraged to recruit controls without any known lumbar spinal impairments of approximately the same age, sex, and activity status from their own environment.

**Table 1 tbl1:** Inclusion and exclusion criteria for the patients.

Inclusion criteria	Exclusion criteria
- Age: at least 18 years old - Voluntary participation - Signed consent - Anatomical lumbar spinal stenosis with characteristic symptoms - Present pain (NRS >3) - Agreement to be treated in the selected rehabilitation facility	- Children and adolescents - Neurodegenerative diseases - Previous spine surgery - Fractures on the lumbar spine (<2 years) - Degenerative lumbar scoliosis (>20°) - Spondylolisthesis > Meyerding 1 (3–14 mm) - ASA classification [18] >4 - Pain (NRS <3) - Orthopedic history at the lower extremities, limiting the patient's activity

For representative sampling, the study collective is self-monitored with regard to the proportion of females included, the preferred post-operative rehabilitation timing, and other parameters that may need to be balanced in periodic meetings of the participating study centers.

### Assessment procedures

2.3

After meeting the inclusion criteria, a brief standard explanation of the aim of the study and the assessments that will be used, participants will be asked to sign the consent form. After completing the medical check-up, which includes demographic information, medical history, anthropometric measurements as well as clinical examinations on a standardized observation sheet, each participant will complete patient-related questionnaires in the same order.

